### Data Analysis

Data will be analyzed following intention-to-treat principles and including all participants as originally assigned, regardless of adherence. Descriptive analysis (mean, SD, median, IQR, and proportion) will be used to describe baseline characteristics by groups. Differences in unintentional injury incidence across 5 timepoints (baseline, 3, 6, 9, and 12 mo) and other outcomes at 2 timepoints (baseline and 12 mo) will be examined using rank-sum tests for ordinal outcomes, chi-square tests for categorical outcomes, and independent 2-sample *t* tests for continuous outcomes. Within-group changes over time will also be evaluated.

Generalized linear mixed models with a Poisson link function will be used to compare the 12-month injury incidence between groups, adjusting for baseline covariates and accounting for clustering at the street or town level. Risk ratios and 95% CIs will be reported. Generalized estimating equations will also be used to assess repeated measures of injury incidence across follow-up timepoints, providing population-averaged estimates while accounting for within-subject and within-cluster correlations. Secondary outcomes, including changes in injury risk levels and caregiver supervision behaviors, will be analyzed using regression models appropriate to the type and distribution of the variable. User engagement indicators will be included as covariates of the effectiveness analysis model.

Two sets of sensitivity analyses will be performed to assess the robustness of findings: (1) per-protocol analyses and (2) models excluding participants with missing primary outcome data. Missing data will be documented and addressed using appropriate statistical methods as needed.

This study will adhere to the CONSORT (Consolidated Standards of Reporting Trials) 2025 [52] statement to perform data analysis and report results.

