### Outcomes

The primary outcome is unintentional injury incidence, calculated as:

$$\frac{Number\;of\;children\;with\;injuries\;during\;the\;12-month\;study\;period}{Total\;number\;of\;children}\times 100\%$$

Injury events will be identified based on established criteria from previous studies [48], defined as any of the following: (1) receiving medical attention at a health care facility and being diagnosed with a specific injury; (2) receiving first aid from a nonmedical responder (eg, family member and teacher), such as wound dressing or bandaging; and (3) missing school for more than half a day due to an injury. We will also compare injury rates at 3-month intervals to assess the effect over time.

In addition, several secondary outcomes will be assessed:

(1) Change in child injury risk level: A 46-item questionnaire will assess children’s risk of unintentional injury, classifying children as low-to-moderate or high risk. The questionnaire was adapted from existing validated instruments and covers 8 common types of injuries: drowning (5 items), road traffic injuries (6 items), choking (6 items), falls (6 items), burns and scalds (6 items), poisoning (5 items), animal bites (5 items), and sharp and blunt object or foreign body injuries (7 items) [43-47].

(2) Change in caregiver supervision behavior score: Caregivers’ caregiver supervision behavior will be measured using a simplified version of a validated 5-item questionnaire, with responses rated on a 5-point Likert scale [49]. Items overlapping with the child injury risk assessment questionnaire were excluded to avoid redundancy.

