### Data Collection

Primary outcome data will be collected every 3 months to minimize recall bias. Secondary outcomes, which are less sensitive to recall bias, will be assessed annually. The baseline survey includes demographic information, child injury history over the past 12 months, caregiver supervision behaviors, and injury risk assessment, selected based on established associations with child injury and potential confounders [51]. All data will be self-reported, collected via the internet-based iCURE system, and securely stored on encrypted databases and hard drives. Caregivers will receive automated reminders followed by telephone follow-up if necessary to improve response rates.

The iCURE system will automatically record user engagement indicators, including (1) whether educational content was viewed, (2) frequency and duration of viewing, (3) messages to iCURE research team, and (4) online subscription to the iCURE WeChat service account.

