## Results

The study received funding in January 2023. Participant enrollment began in August 2024 and was completed in February 2025. A total of 6701 individuals completed baseline data, with 3110 allocated to the intervention group and 3591 to the control group (Table 2). The two groups somewhat differed in child age, place of residence, caregiver’s age, and education—the control group had higher proportions of children aged 3 to 5 years (69.7% vs 57.6%), residing in urban areas (61.3% vs 57.4%), caregivers aged 30 years and older (81.2% vs 74.9%) and receiving high or vocational school education and higher (85.7% vs 80.2%) than the intervention group (*P*<.05). The baseline 12-month injury incidence reported by caregivers was 8.86% (7.96-9.84) in the control group and 9.04% (8.06-10.11) in the intervention group.

By May 2025, 5,842 (87.2%) participants had completed the first follow-up survey.

**Table 2. T2:** Number of recruited caregivers and children by demographic characteristics (%).

Variables	Overall, n (%)	Control, n (%)	Intervention, n (%)	*P* value
Total	6701 (100.0)	3591 (100.0)	3110 (100.0)	
Child gender				>.99
Girl	3147 (47.0)	1686 (47.0)	1461 (47.0)	
Boy	3554 (53.0)	1905 (53.0)	1649 (53.0)	
Child age (years)				<.001
1	1047 (15.6)	468 (13.0)	579 (18.6)	
1-2	1358 (20.3)	619 (17.2)	739 (23.8)	
3-5	4296 (64.1)	2504 (69.7)	1792 (57.6)	
Place of residence				.001
Urban	3988 (59.5)	2203 (61.3)	1785 (57.4)	
Rural	2713 (40.5)	1388 (38.7)	1325 (42.6)	
Caregiver’s gender				.09
Female	5400 (80.6)	2922 (81.4)	2478 (79.7)	
Male	1301 (19.4)	669 (18.6)	632 (20.3)	
Caregiver’s age (years)				<.001
＜30	1458 (21.8)	677 (18.9)	781 (25.1)	
30-39	4343 (64.8)	2408 (67.1)	1935 (62.2)	
≥40	900 (13.4)	506 (14.1)	394 (12.7)	
Number of children in the family				.51
1	3010 (44.9)	1627 (45.3)	1383 (44.5)	
≥2	3691 (55.1)	1964 (54.7)	1727 (55.5)	
Caregiver’s education				<.001
Junior high school or lower	1131 (16.9)	514 (14.3)	617 (19.8)	
High or vocational school	1493 (22.3)	816 (22.7)	677 (21.8)	
College or higher	4077 (60.8)	2261 (63.0)	1816 (58.4)	

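### Baseline injury incidence (12-month look-back) is listed as a timepoint beside 3-monthly follow-up values, so a within-arm change from baseline would show a large fall with no intervention effect

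*Protocol article*

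**What the plan says.** All places are in the protocol article.

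- **Data Analysis** lists five timepoints for one injury measure: "Differences in unintentional injury incidence across 5 timepoints (baseline, 3, 6, 9, and 12 mo"). Chi-square, rank-sum and independent-sample *t* tests are named for this sentence, which also covers the other outcomes at baseline and 12 months. It is followed by: "Within-group changes over time will also be evaluated". No outcome is exempted.
- **Data Collection** defines what baseline measures: "child injury history over the past 12 months". For follow-up it says: "Primary outcome data will be collected every 3 months to minimize recall bias".
- **Outcomes** defines the primary outcome as the proportion of children injured over the 12-month study period, and adds: "We will also compare injury rates at 3-month intervals to assess the effect over time".
- **Results** already reports the baseline measure as a 12-month quantity: "The baseline 12-month injury incidence reported by caregivers was 8.86% (7.96-9.84) in the control group" and "9.04% (8.06-10.11) in the intervention group".

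The article nowhere converts these values to child-time, annualises them or otherwise puts them on a common window.

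**The concern.** The proportion of children injured at least once rises with the length of the window. A 12-month proportion and a 3-month proportion are different quantities even when the underlying rate is the same. They also rest on different recall periods, which the article itself treats as a source of bias. Listing them as five timepoints of one measure, and then planning within-group changes over time, invites a before-after comparison whose result is driven by window length.

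At stake is a reported drop in injuries within the intervention arm, larger than the 25% reduction assumed in the Sample Size section and apparently very precise, that a reader could take for benefit. A similar drop would appear in the control arm, but a within-group result is often quoted on its own.

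**Working it through.** The article gives no figure for a within-arm change, so there is none to reproduce. The check asks what change would appear with no intervention effect.

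**Inputs**
- Baseline 12-month incidence (Results): control 8.86%, intervention 9.04%.
- Arm sizes (Results): 3591 control, 3110 intervention.
- Planning incidence 15.5% over 12 months and design effect 1.5 (Sample Size).
- Follow-up window of 3 months: implied by Outcomes and Data Collection, not stated as a recall period.

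**Step 1. Constant hazard, equal reporting.** Incidence over m months is p_m = 1 − (1 − p_12)^(m/12).
- Intervention: 1 − (1 − 0.0904)^(1/4) = 0.0234. Fall = 1 − 0.02341/0.0904 = 74.1%.
- Control: 1 − (1 − 0.0886)^(1/4) = 0.0229. Fall = 1 − 0.02293/0.0886 = 74.1%.
- At the planning rate of 15.5%: 0.0412 over 3 months, a fall of 73.4%.

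**Step 2. How significant it would look.** For one baseline value against one 3-month value, unpaired, with all children seen both times, z = (p_12 − p_3) / √[2 p̄(1 − p̄)/n], where p̄ is the mean of the two.
- Intervention: z ≈ 11.4. Control: z ≈ 12.1.
- Dividing by √1.5 for the design effect leaves about 9.3 and 9.9.

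These values ignore the pairing of observations within children and show only the order of magnitude.

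**Step 3. Other assumptions.** The article gives no figures for these, so they are ranges.
- *Injury-prone children.* With gamma frailty of mean 1 and variance θ, Λ = [(1 − p_12)^(−θ) − 1]/θ and p_3 = 1 − (1 + θΛ/4)^(−1/θ). From 8.86%:

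| θ | 3-month incidence | Fall |
|---|---|---|
| 0.5 | 2.33% | 74% |
| 2 | 2.45% | 72% |
| 5 | 2.72% | 69% |
| 10 | 3.18% | 64% |

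- *Under-recall at baseline.* If the true 12-month risk is 15.5% and is reported fully over 3 months, p_3 = 4.12%. The fall is 1 − 0.0412/0.0886 = 53% (control) and 1 − 0.0412/0.0904 = 54% (intervention).

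**Step 4. If follow-up values are cumulative from enrolment.** The Step 1 formula with m = 3, 6, 9, 12 gives 2.34%, 4.63%, 6.86% and 9.04% in the intervention arm. The falls are 74%, 49%, 24% and 0%, and the control arm gives the same rounded falls. Only month 12 matches the baseline window.

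**Step 5. Infants.** Participant Recruitment sets no lower age limit, so children under 1 year have less than 12 months of history. The youngest row of Table 2 is printed as 1, next to a row for 1-2, and so is probably under 1 year. It holds 18.6% of intervention and 13.0% of control children. A shortened look-back lowers recorded baseline incidence, which makes the artefactual fall smaller. If the row is read correctly, baseline exposure also differs somewhat between arms.

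**The case against.** The strongest reply is that the five-timepoint sentence describes comparisons between arms. The tests named are for independent samples, and within-group change is introduced afterwards as something additional. At any one timepoint both arms share the same window, so its length cancels. This stands: the sentence does not by itself commit the trial to a longitudinal test that includes baseline.

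A reader might infer that the repeated-measures model or the primary result is contaminated. The text does not support that. The generalized estimating equations are described as running across follow-up timepoints, and the mixed model compares 12-month incidence between groups.

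It can also be said that the within-group sentence is unspecific. It could refer to the secondary outcomes at baseline and 12 months, to the four follow-up intervals, or to a comparison of matched 12-month windows, all of which are free of the window problem, and the full protocol or analysis plan may settle which. This stands in part. The text admits valid readings, so dropping every within-group injury analysis would go too far. But the sentence directly follows a list that names baseline as an injury timepoint and excludes nothing. This is therefore a statement that would mislead if followed, not merely a detail left out.

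Finally, 74% is not a certain figure. It needs a constant hazard and equal reporting over 12 and 3 months, and the 3-month window is inferred. That is correct, and the ranges above reflect it. Under the alternatives examined, a 3-month value still falls more than 50% below baseline.

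**Conclusion.** The point holds for a supporting analysis. As written, a within-arm change in injury incidence from baseline to a 3-month follow-up value would show a large fall with no intervention effect: about 74% in each arm at constant hazard and equal reporting, and roughly 53% to 74% under the recall and frailty assumptions examined. If the follow-up values are cumulative, the mismatch shrinks with time and disappears at month 12. Between-arm tests at a single timepoint, the primary 12-month comparison and the estimating-equation analysis over follow-up are untouched. It should be corrected before follow-up data are analysed, but it does not threaten the trial's main conclusion.

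**What to change.** Reword the Data Analysis section as follows.

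1. Remove baseline from the injury-incidence time series, leaving 3, 6, 9 and 12 months, and state whether those values are interval or cumulative.
2. Use the baseline 12-month injury history as a covariate and to describe the arms at baseline.
3. Limit within-group change in injury to the four equal follow-up intervals.
4. If a before-after display is wanted, set baseline 12-month incidence against cumulative 12-month follow-up incidence, descriptively, with a caveat on recall length and on the incomplete look-back for infants. With matched windows, the artefact from window length is 0% under the constant-hazard calculation.

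The cost is wording only. No new data are needed, and the primary analysis and sample size do not change.

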### Sample Size

Previous research reported a 12-month incidence of unintentional injury of 15.5% among children younger than 6 years of age in Changsha [33]. We hypothesize that the proposed mHealth intervention will reduce the injury incidence rate by 25% [34], with a design effect of 1.5 for the cluster sampling [35]. We also very conservatively assume 30% loss to follow-up [36]. Given these assumptions, a minimum sample size of 5178 children is needed to achieve 80% statistical power at a .05 significance level with a 1:1 allocation ratio between intervention and control groups (G*Power 3.1.9.7). Given that the actual values of certain parameters (eg, incidence rate and effect size) may be somewhat lower than assumed [28,34], we empirically expanded the sample size to recruit approximately 5600 children, with (2800 children from urban areas and 2800 from rural areas, including at least 350 children from each selected urban street and 700 from each rural town) within the constraints of available research resources. The 1:2 recruitment ratio of urban streets and rural towns is based on prior field experience, which suggests greater recruitment challenges in urban areas compared to rural ones.

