### Randomization and Blinding

Randomization will be conducted at the street or town level to minimize potential contamination. Each street or town will be randomly assigned to either the intervention or control group, stratified by administrative division, using a random number sequence generated by R 4.4.1 software (R Core Team). The group allocation will remain concealed from both participants and the researcher conducting data analysis.

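### The unadjusted chi-square, t and rank-sum tests between arms ignore randomisation by 12 streets or towns, and the secondary outcomes have no stated cluster-adjusted analysis

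*Protocol article*

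**What the plan says.** Under Randomization and Blinding: "Randomization will be conducted at the street or town level". Participant Recruitment gives 12 such units in five districts, and allocation is stratified by administrative division. The Sample Size section inflates the requirement "with a design effect of 1.5 for the cluster sampling".

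Data Analysis then sets out two layers of comparison.

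- **Simple tests.** Differences in injury incidence at baseline, 3, 6, 9 and 12 months, and in other outcomes at baseline and 12 months, "will be examined using rank-sum tests for ordinal outcomes, chi-square tests for categorical outcomes" and independent two-sample t tests for continuous outcomes. No allowance for clustering is attached. Within-group change is mentioned separately, so these are between-group tests.
- **Models.** A Poisson mixed model compares 12-month incidence and accounts for street or town. GEE handle repeated injury incidence and account for within-subject and within-cluster correlation. The secondary outcomes (risk level and supervision score) get regression models chosen by variable type and distribution, with nothing said about clustering.

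The Results section prints P values for baseline characteristics in Table 2, and baseline 12-month incidence as "8.86% (7.96-9.84) in the control group and 9.04% (8.06-10.11) in the intervention group".

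**The concern.** A chi-square, t or rank-sum test on individual children uses a variance that omits variation between streets and towns. When whole streets are allocated, that variation goes straight into the difference between arms, so the test rejects too often when the intervention does nothing.

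Two sets of results are exposed. The Outcomes section makes comparison at 3-month intervals an explicit aim, so a wave-specific P value from an unadjusted test could be reported as an early or transient effect when it reflects differences between streets. For the secondary outcomes there is no stated cluster-adjusted result to set against the simple test. The protocol names these tests itself, so this is not a detail left to a fuller analysis plan.

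**Working it through.** **Inputs from the protocol article**
- Sample Size: control incidence 15.5%; 25% relative reduction, so 0.155 × 0.75 = 11.625%; design effect 1.5; 30% loss; 80% power; significance level .05 (sidedness not stated).
- Participant Recruitment: 12 clusters.
- Results: 6701 children, 3591 control and 3110 intervention.

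**1. Reproduce the plan's own figure.** The plan states "a minimum sample size of 5178 children is needed to achieve 80% statistical power". The two-sided two-proportion formula with pooled variance gives 1225 per arm. Then 1225 × 1.5 / 0.70 = 2625 per arm, or 5250 in total, which is 1.4% above 5178. An arcsine version gives 5230 and an unpooled one 5238. A one-sided version gives 4136 and does not fit. The stated size is therefore close to a two-sided 5% test with the design effect applied, so the plan itself expects the variance of the arm difference to be 1.5 times the independent-sample value.

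**2. True error of an unadjusted test.** If the variance is inflated by a design effect DE, the actual two-sided error of a nominal 5% test is

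2 × [1 − Φ(1.96 / √DE)]

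At DE = 1.5: 1.96 / √1.5 = 1.600, giving 0.1095, or 2.19 times nominal. A beta-binomial simulation (12 equal clusters, six per arm, 200,000 replicates per setting) gave 0.109 in each of three settings: 15.5% incidence with 302 or 466 children per cluster, and 9% with 558.

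**3. Intracluster correlation (ICC) implied by the design effect.** The article gives no ICC. From DE = 1 + (m − 1) × ICC, DE = 1.5 means ICC = 0.5 / (m − 1):
- m = 5178 × 0.70 / 12 ≈ 302 gives 0.0017.
- m = 6701 / 12 ≈ 558 gives 0.0009.

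As an assumed range at 558 children per cluster:

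| ICC (assumed) | DE | True error of a nominal 5% test |
|---|---|---|
| 0.0005 | 1.28 | 8.3% |
| 0.001 | 1.56 | 11.6% |
| 0.005 | 3.79 | 31% |

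**4. Effect of stratification.** Balancing arms within districts removes between-district variation from the arm difference, which steps 2 and 3 ignore. A simulation with eight clusters of 350 and four of 475, ICC 0.0017 and an assumed even split within five districts gave errors of 13.5%, 11.1%, 8.9% and 6.9% when 0%, 25%, 50% and 75% of the between-cluster variance lay between districts. Those shares are assumptions. The starting value exceeds 11% because the size-weighted mean cluster is about 400, so DE = 1 + 399.5 × 0.0017 ≈ 1.68.

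**5. What has been printed so far.** Table 2 reproduces with ordinary chi-square tests, continuity-corrected for the 2 × 2 tables:

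| Characteristic | Recomputed P | Printed P |
|---|---|---|
| Child gender | 1.00 | >.99 |
| Residence | .0011 | .001 |
| Caregiver gender | .086 | .09 |
| Number of children | .507 | .51 |
| Child age, caregiver age, education | <.001 | <.001 |

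With counts inferred from the percentages (318/3591 and 281/3110), continuity-corrected Wilson intervals for independent observations are 7.96–9.84 and 8.06–10.11, exactly as printed. The printed half-widths are (9.84 − 7.96)/2 = 0.94 and (10.11 − 8.06)/2 = 1.03 points. If the design effect of 1.5 is carried over to baseline incidence, the half-widths become 1.96 × 0.474 × √1.5 = 1.14 and 1.96 × 0.514 × √1.5 = 1.23 points.

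**The case against.** The strongest reply is that the comparisons that matter are already cluster-adjusted. The mixed model covers 12-month incidence, GEE cover the follow-up waves, and the abstract ties effectiveness to those two methods without mentioning the simple tests. The risk ratios and confidence intervals that the plan promises come directly after the mixed model. All of this stands. A reader might infer that the primary 12-month result has a doubled false-positive rate, or that its intervals will be too narrow; the document does not support either. The abstract also shows, though not as a formal rule, which analysis carries the effectiveness claim.

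A reader might also take error rates of 16% to 26% or more as the plan's own. They are not: they need design effects of 2 to 3 (16.6% and 25.8%) or ICCs such as 0.005, none of which the document states. The design effect of 1.5 is given for 12-month incidence; its use for 3-month incidence, risk level, supervision score or baseline incidence is an assumption. Stratification by division could bring the error below 11%.

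Table 2 and the baseline intervals describe the sample and are not the effectiveness analysis. They show that unadjusted methods have been used in print, but changing them is a reporting matter.

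It can also be said that the secondary-outcome models may be specified in a plan not shown. That would excuse a missing detail. It does not excuse naming, for those same outcomes, tests that assume independence.

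**Conclusion.** The point holds for the unadjusted between-group tests. At the plan's own design effect their true error is about 11% against a nominal 5%, before any reduction from stratification; for outcomes other than 12-month incidence, that design effect is assumed. The direction is not in doubt: any positive variation between streets within districts inflates the error.

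The consequence differs by outcome. For 12-month injury incidence the mixed model is unaffected. For the 3-, 6- and 9-month comparisons, an invalid P value would stand beside a GEE that does account for clustering. For risk level and supervision score, no cluster-adjusted analysis is stated anywhere in the article, and this is where correction matters most.

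**What to change.** - Remove the chi-square, t and rank-sum tests as between-group inference. Show those summaries by arm and timepoint descriptively, without P values.
- Take the wave-specific injury contrasts from the planned GEE or mixed model.
- State that the secondary-outcome comparisons account for street or town clustering with a method suited to 12 clusters, for example a mixed model with a small-sample correction, or a cluster-level t or permutation test.
- Report Table 2 without P values, and give baseline incidence intervals that allow for clustering.

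The cost is analysis-plan wording and some reporting; recruitment, data collection and participants are untouched. The article reports follow-up only as far as the first survey, so on its account the change can precede the 12-month analysis. The downside is wider, correct intervals.

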### Implementation Protocol

During routine consultations, primary health care providers will assist caregivers in registering for the iCURE WeChat service account. Upon registration, all caregivers will complete a questionnaire providing demographic information, their child’s injury history, and an injury risk assessment survey.

Caregivers randomly assigned to the intervention group will then receive the full version of the iCURE program, including real-time feedback, tailored educational content, and access to the Q&A module. The control group will access a simplified version involving completion of assessment surveys that are used only for data collection; they will receive no feedback, education, or supplemental materials. Both groups will continue to receive routine safety education provided by preschool teachers and primary health providers. Group allocation is detailed in Table 1. Details regarding the timeline for recruitment and intervention period are shown in Figure 3.

**Table 1. T1:** Functions of iCURE (Intelligent Child Unintentional-Injury Reduction & Education) used by intervention group and control group.

Functions	Intervention group	Control group
Data collection	✓	✓
Injury risk assessment	✓	✓^a^
Instant feedback	✓	
Tailored education	✓	
Interactive questions and answers	✓	

a Control group will complete the injury risk assessment for data collection purposes, with no risk evaluation reports provided.

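### As written, post-randomisation engagement indicators enter the effectiveness model, so its arm coefficient would not be the intention-to-treat risk ratio

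*Protocol article*

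**What the plan says.** The Data Analysis section opens with the principle: "Data will be analyzed following intention-to-treat principles and including all participants as originally assigned, regardless of adherence". The primary between-group analysis follows: "Generalized linear mixed models with a Poisson link function will be used to compare the 12-month injury incidence between groups". The article then describes what this model takes into account besides arm: "adjusting for baseline covariates and accounting for clustering at the street or town level". The effect measure is fixed too: "Risk ratios and 95% CIs will be reported". Generalized estimating equations for the repeated measures and regressions for the secondary outcomes come next, and that paragraph closes with "User engagement indicators will be included as covariates of the effectiveness analysis model".

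The Data Collection section defines the indicators: "The iCURE system will automatically record user engagement indicators, including (1) whether educational content was viewed, (2) frequency and duration of viewing", then messages to the research team and subscription to the WeChat service account.

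The Implementation Protocol section says of control caregivers that "they will receive no feedback, education, or supplemental materials". Table 1 agrees: tailored education, instant feedback and the question-and-answer function are ticked for the intervention group only.

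The Abstract (Methods) names the Poisson mixed models and the estimating equations as the means of assessing effectiveness, under intention-to-treat.

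**The concern.** Engagement is a consequence of allocation. An intention-to-treat model can adjust for what was known at baseline, but adjusting for what families did with the intervention conditions on part of the route by which it may work.

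The viewing indicators make this acute because no control family can score above zero on them. The arm term is then identified only by intervention families with zero viewing, set against every control. Any benefit that comes through viewing passes to the engagement coefficient.

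The non-viewers are also a self-selected group. The article gives reasons to expect a link between engagement and injury risk: under Key Components and Content, higher-risk children are sent content 2 or 3 times a week and low-risk children once, and under Strategies to Enhance Engagement, viewing earns points. Adjustment can therefore bring back confounding that randomisation had removed. At stake is the between-group risk ratio for the primary outcome, and the secondary-outcome effects if the same rule is applied there.

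**Working it through.** **Inputs from the article.** Control 12-month incidence 15.5% and a 25% reduction (Sample Size); 3110 intervention and 3591 control children (Results). The target risk ratio is 0.75, or 15.5% against 0.75 × 15.5% = 11.625%.

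**The plan's own figure.** These rates need 1225 children per arm (two-sided 0.05, 80% power). 2 × 1225 × 1.5 / 0.70 = 5250, against 5178 stated, a difference of 1.4%. So 0.75 is the effect the trial was sized for. The sample size is not affected by this point.

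**Assumption not in the article.** The share v of intervention caregivers who view content. I take 50% and 70%, and 90% as an upper case.

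**1. What the arm term estimates.** Take log(risk) = a + b·arm + c·viewed, with viewed = 0 for all controls. Then exp(b) is the risk in non-viewing intervention children divided by the risk in all controls. This follows from the coding and needs no assumption about the effect.

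**2. Limiting case: the whole effect runs through logged viewing and viewers are not selected.** The intention-to-treat ratio is v·r + (1 − v) = 0.75, where r is the risk ratio in viewers.
- v = 0.5: r = (0.75 − 0.50)/0.5 = 0.50
- v = 0.7: r = (0.75 − 0.30)/0.7 = 0.64
- v = 0.9: r = (0.75 − 0.10)/0.9 = 0.72

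Non-viewers have the control risk, so exp(b) = 1.00 each time.

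**3. Partial mediation, no selection.** Let d be the ratio acting outside logged viewing, with d × [v·r + (1 − v)] = 0.75. Then exp(b) = d, which lies between 0.75 (nothing through viewing) and 1.00 (everything through viewing). If the effect is split equally on the log scale, d = √0.75 = 0.87.

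**4. Selective viewing.** A Poisson log-link model was simulated without clustering, with five runs of 200,000 children per scenario and nominal v of 50%, 70% and 90%. A latent factor raised the log-odds of viewing by 1 per SD and, where viewing was selective, multiplied injury risk by 0.8 or 1.25 per SD. Any effect acted only through viewing.

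| Scenario | Arm RR, engagement left out | Arm RR, viewed as covariate |
|---|---|---|
| Planned effect, viewing unrelated to risk | 0.75 to 0.76 | 1.00 to 1.02 |
| Planned effect, selective viewing | 0.73 to 0.77 | 0.84 to 1.20 |
| No effect, selective viewing | 1.00 | 0.83 to 1.20 |

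The last row shows that selection alone can produce an apparent benefit or harm.

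**5. Precision.** With equal arms, the squared correlation of arm and viewed is v/(2 − v). In a linear approximation the variance inflation is (2 − v)/(2 − 2v).
- v = 0.5: correlation √(0.5/1.5) = 0.58; inflation 1.5/1.0 = 1.5; SE × 1.22
- v = 0.7: correlation √(0.7/1.3) = 0.73; inflation 1.3/0.6 = 2.17; SE × 1.47

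Cross-check with the enrolled numbers, Poisson variance and the limiting case of step 2. Without the covariate, SE = √(1/(3591 × 0.155) + 1/(3110 × 0.11625)) = 0.067. With it, the second term becomes 1/(3110 × (1 − v) × 0.155):
- v = 0.5: SE 0.077, ratio 1.1
- v = 0.7: SE 0.093, ratio 1.4
- v = 0.9: SE 0.150, ratio 2.2

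With no effect, the starting SE is √(1/(3591 × 0.155) + 1/(3110 × 0.155)) = 0.062, and the ratios at 50% and 70% are 1.2 and 1.5.

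**The case against.** The strongest reply is that a supplementary model was meant. The mixed-model sentence names only baseline covariates, which engagement is not. The engagement sentence comes after the estimating equations and the secondary outcomes and does not name the mixed model. This has some force: the text does not prove that the sponsor will report an engagement-adjusted primary result. But nothing restricts the sentence. The Abstract identifies the mixed models and estimating equations as the effectiveness analyses, and engagement adjustment is not among the two listed sensitivity analyses. At best, two sentences of one paragraph conflict.

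A second reply concerns size, and it stands. iCURE also works through instant feedback and risk reports, the question-and-answer module, themed activities, and materials shared in WeChat groups. These may act outside logged viewing and leave part of the effect in the arm term.

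A reader might also infer three stronger things that the article does not support:
- That nearly all the indicators exist only in the intervention arm. This is clear only for viewing. Caregivers in both arms register for the service account, so subscription exists in both, and the article does not say that controls cannot send messages. Subscription during follow-up is still post-randomisation.
- That engagement is almost collinear with arm. Correlations of 0.58 to 0.73 do not amount to that; it would take viewing of about 90% or more.
- That this covariate is what would unblind the analyst. The planned per-protocol analysis would plausibly need adherence data anyway, and the point does not depend on it.

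**Conclusion.** The point holds for the plan as written. Engagement recorded after randomisation is made a covariate of the effectiveness model without restriction. Because viewing is structurally zero in controls, the arm coefficient of that model is not the intention-to-treat risk ratio. This contradicts both the commitment to analyse regardless of adherence and the baseline-only specification of the mixed model. The change of estimand follows from the coding alone.

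The size depends on assumptions. At 50% to 70% viewing without clustering, the standard error rises about 1.2 to 1.5 times. The arm risk ratio moves from 0.75 to about 1.00 only if the whole planned effect runs through logged viewing. With partial mediation and no selection it lies between the two. With selective viewing it was 0.84 to 1.20 under the planned effect and 0.83 to 1.20 under no effect, in the scenarios tried.

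It would be too strong to conclude that the trial's effect will disappear or that the reported ratio is bound to be wrong. The first requires full mediation; the second requires that the sentence be applied to the primary model.

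**What to change.** Replace the engagement sentence with a statement that the primary and secondary effectiveness models (the mixed model, the estimating equations and the secondary-outcome regressions) contain only arm, the stratification factor, covariates measured at baseline and the clustering terms.

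If engagement is of interest, put it in a separate analysis labelled exploratory, for example dose-response within the intervention arm, and state that it does not estimate the randomised effect. The sentence need not be dropped altogether if it is confined in this way.

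The cost is a sentence or two in the analysis plan. No new data and no change in sample size are needed. The change should be recorded before outcomes are analysed by arm.
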